### Recruitment

Youth will be recruited from community and school programs serving young people in or transitioning from foster care. Recruitment and enrollment will occur on a rolling basis during years 2 and 3 and the first quarter of year 4 across 24 California counties, including postsecondary on-campus support programs such as Guardian Scholars and NextUp. Each collaborating site designates a recruitment ambassador, typically an adult supporter who works directly with foster youth. The primary criterion for ambassadors is that they are staff members who meet individually and have direct contact with youth who meet study eligibility criteria. The study team trains all recruitment ambassadors and provides them with a standardized protocol that includes approved materials (recruitment flyers, brief videos explaining the study, a frequently asked questions document, and recruitment scripts). Upon completion of the training, ambassadors promote the study at their site, share the opportunity with youth who come in for direct services, and incorporate the study into the site’s normal outreach mechanisms (eg, newsletters, direct mailing, and virtual and hard copy posters with a QR code). Recruitment ambassadors are trained to only present the study opportunity to youth who meet the study criteria based on their knowledge of the young people. Youth enroll in the study through an enrollment portal at partner sites (with ambassadors supporting youth through the process), which involves completing a screener and reviewing and signing the study consent form. Youth are also asked to input a recruitment code (which is unique to each recruitment ambassador), which allows the study team to track recruitment and confirm eligibility.

### Consent and Assent Process

We received a waiver of parental permission from the ETR institutional review board for youth ages 16‐17 years, who will complete an assent form written at an eighth-grade reading level, while youth ages 18‐19 years will complete a consent form at the same readability level. Both forms are collected online to align with the fully mobile nature of the intervention. The assent and consent forms include 3 multiple-choice questions to assess young people’s understanding of what they are being asked to do. If youth mark a question incorrectly, a clarifying message will be provided to ensure they have the information needed to make their decision. At the end of the consent form, youth will be asked to indicate their decision of whether they want to take part or not or if they would like to talk with a study team member to get more information before deciding. Youth who decline participation will be thanked for their consideration and will not be contacted again. Youth who say they would like to talk with a study team member will be contacted by a study team member within 2 business days to provide clarifying information. These youth would then be allowed to make their decision online.

### Randomization

Randomization takes place after young people submit their baseline survey using the randomizing feature in Qualtrics with a 50‐50 allocation fraction. More specifically, 50% of participants will be allocated to the intervention group and 50% of participants will be allocated to the comparison group. The study evaluator oversees and manages the randomization protocol. Once randomized, youth are automatically re-directed to the Next4You log in page, based on their assigned conditions along with steps for logging in and establishing their accounts.

### Data Collection Methods

#### Baseline Survey

The evaluation of Next4You will rely on a confidential youth self-report survey assessing knowledge, attitudes, beliefs, and behaviors related to sexual health through web-based surveys administered via the Qualtrics platform. Young people receive a unique link via email to the survey immediately after affirming their assent to study participation. The study team will follow up with youth who do not complete the baseline survey by sending up to 3 texts and 2 additional emails over the course of approximately 3 weeks, each with the unique link to their baseline survey, and an offer to answer questions or support in completing the survey. The study team will then engage the recruitment ambassador for assistance in reaching out to the youth and encouraging them to complete the survey.

Participants will be randomized after the baseline survey and are automatically re-directed at the end of the survey to access their assigned intervention condition. The baseline survey is estimated to take approximately 25 minutes to complete. Participants receive a gift card worth US $40 for filling out the baseline survey.

#### Preparing for Follow-Up Surveys

One month prior to sending each follow-up survey, youths are asked to provide the study team with their latest contact information. Each youth is contacted simultaneously at their last known phone number and email address—one of which has usually not changed in the 3- and 6-month periods since their last follow-up survey. This outreach serves to both remind youth that a follow-up survey will be sent to them in the next few weeks and maintain the most recent, preferred contact information to reach the youth when their next survey is sent. Doing so 1 month in advance gives youth time to reply or receive up to 3 reminders if needed. This confirmation of contact information request is associated with a US $10 e-gift card when the youth replies to the study team with their current contact information.

#### Follow-Up Surveys (3 and 9 Months)

Both follow-up surveys are administered online using procedures like those used at baseline. The study team will use a multimethod outreach process to contact youth who do not respond to the surveys. In the first phase, the study team will send up to 3 simultaneous texts and emails to encourage nonrespondents to complete the survey. During the second phase, youth who have not responded will receive up to 2 calls (with voicemails) from the study team during the following week. If youth have not completed the survey during the second phase, the study team will wait 1 week before implementing the third phase of outreach, which involves engaging with the study recruitment ambassadors for assistance in reaching out to the youth and encouraging them to complete the survey. At all outreach attempts by the study team, participants are provided with the study team’s email and phone for any questions or need for assistance in completing the survey.

#### Implementation Evaluation Data Collection

Given the intervention is fully mobile, our implementation evaluation data collection focuses on four areas related to fidelity that have been found to influence dose and treatment effects in mobile interventions [37]: (1) amount (count of lessons completed), (2) frequency (counts of user sessions and patterns of use), (3) duration (amount of time spent in each module and lesson), and (4) depth (total content and engagement as a percentage of all available content). These data will be collected from the web platform directly. We will also conduct selected postintervention interviews to gather qualitative data on user experiences during the study.

#### Retention

The study team will implement a comprehensive participant tracking and retention strategy designed to maximize response rates and minimize attrition across all follow-up periods. This approach includes allocating sufficient resources for incentives, dedicating staff time to personalize follow-up, and conducting multiple outreach attempts to nonrespondents. Consistent with intent-to-treat (ITT) principles, all youth enrolled in the evaluation will be tracked and will receive retention-focused outreach, regardless of level of engagement or participation.

Participants will receive e-gift card incentives for completing evaluation surveys, verifying or updating contact information, and completing intervention activities. In total, youth may earn up to US $315 for completing all activities. Incentive amounts include US $40 for the baseline survey, US $60 each for the 3- and 9-month follow-up surveys, US $10 per response (up to 2 times) for confirming or updating contact information, and up to US $125 for completing intervention activities. Incentive values were informed by a consultant with lived and professional experience in the foster care system to ensure that compensation reflects and honors participants’ time and expertise.

Retention in the intervention group platform will include gamification features such as badges and a point-based reward system that allows for points to be converted into electronic gift cards. Additionally, push factor text and email notifications will be used to promote engagement. For example, if there has been no activity for at least 3 days, an automatic notification will go out to participants inviting them to log onto the platform and continue earning points through the completion of lessons. Youth assigned to the comparison group platform will receive equivalent total incentives for completing a minimum of 12 online pamphlets [38-49] on promoting healthy eating and nutrition, sleep, exercise, and reducing stress and anxiety. The total amount of incentives that youth may receive is the same for both study groups.

### Outcomes

#### Primary Outcome

The primary outcome of this study is the impact of the 4-week Next4You intervention on contraceptive use among youth in foster care. Specifically, this study will examine the prevalence of participants who report either abstaining from sex or using c condoms during vaginal or anal sex in the past 3 months, compared with participants provided access to a mobile-responsive website containing only general wellness resources (sleep, nutrition, stress and anxiety, and exercise). This outcome will be assessed using data from the 3-month postintervention follow-up survey.

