**Secondary research questions**

*Nine months following the intervention:*
1. What is the effect of the 4-week Next4You intervention on the prevalence of choosing abstinence or using condoms among youth in foster care who had vaginal or anal sex in the past 3 months?
*Three and nine months following the intervention period:*
2. What is the effect of the 4-week Next4You intervention on rates of condomless vaginal or anal sex?3. What is the effect of the 4-week Next4You intervention on sexual consent self-efficacy?4. What is the effect of the 4-week Next4You intervention on sexual communication self-efficacy?5. What is the effect of the 4-week Next4You intervention on condom use attitudes?6. What is the effect of the 4-week Next4You intervention on contraceptive use attitudes and beliefs?7. What is the effect of the 4-week Next4You intervention on experiences with equity and power balance in relationships?8. What is the effect of the 4-week Next4You intervention on knowledge of health care rights and location of services?9. What is the effect of the 4-week Next4You intervention on contraceptive use (specifically experience with condom errors)?10. What is the effect of the 4-week Next4You intervention on knowledge of educational rights and programs?11. What is the effect of the 4-week Next4You intervention on financial literacy knowledge?

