Communication	7	“I” versus “you” statements; preparing for having difficult conversations; strategies for managing emotions that may surface during difficult conversations; strategies for de-escalating conversations; strategies for active listening to improve communication skills.
Respecting Self and Partners	7	Self-love and self-worth; affirmative consent; what respecting a partner includes; personal boundaries; strategies for navigating different personal boundaries; gender and gender identity.
Contraception	5	Condom use and steps; common methods of birth control; withdrawal from a harm reduction perspective; contraception rights; options if methods of contraception fail.
Building Wealth and Wellness	12	Passion and purpose; educational rights; college transition and support services; financial rights; coping skills; financial aid options; trauma—building resilience and navigating past trauma; mental health; budgeting; body image.

The Next4You platform includes a total of 50 microlessons, and participants earn points for each completed lesson. To motivate early engagement with the website, participants receive a US $25 e-gift card upon completing 5 lessons. Subsequent points are banked, and the remaining incentive amount is distributed at the end of the 4 weeks, based on the total amount of points earned. Participants may earn up to US $100 in e-gift cards for completing all 50 microlessons. In addition to lesson completion, participants can earn up to US $25 in bonus incentives through all 4 achievement badges: Start Up, On Fire, My Faves, and Consistency. In total, participants may earn a maximum of US $125 in e-gift cards over the 4-week program period.

The online platform will collect paradata in the form of timestamps and counts of user sessions for all actions performed by each user, thereby allowing for calculation of the time spent engaging with the intervention (including total time spent on each microlesson, modules, and engaging with various activities and resources), frequency of logins, and the amount of completed content. Users will be automatically logged out after approximately 10 minutes of inactivity to protect privacy and reduce the likelihood of inflated duration data. The evaluation will use the duration data to conduct exploratory analyses examining differing levels of exposure and the relation to study outcomes.

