### Sample Size and Power Analyses

Our proposed sample of 500 young people (with a 1:1 allocation to each condition) would result in the Next4You evaluation being powered to identify effects in the range of small to “substantively important” (ie, 0.25 SDs, in accordance with the WWC standards) [36]. The power analysis estimates were obtained and validated via Optimal Design Plus Empirical Evidence software and the HHS Office of Adolescent Health’s Teen Pregnancy Prevention MDI and MDES calculator. The estimates were developed based on the following parameters in accordance with the funder evaluation standards: simple randomization at the individual level; 25% attrition rate; type I error rate of 5%; type II error rate of 20% (ie, power of 0.80); 2-sided hypothesis test; 50% probability of assignment to the treatment group; outcome prevalence of 50%; 25% of the outcome variance is explained by covariates. The impact model will include the baseline measure of the outcome and age or grade level, sex, and race and ethnicity as covariates consistent with funder requirements. The study team will use a combination of data- and theory-driven approaches to select additional covariates for inclusion in the model to further improve the precision of the impact estimates.

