#### Secondary Outcomes

The secondary outcomes will examine the impact of the 4-week Next4You intervention, compared with a mobile-responsive website on wellness topics, on a range of sexual and reproductive health and well-being outcomes among youth in foster care. Specifically, analyses will assess effects on condom use behaviors, condomless sex, and condom errors; self-efficacy related to sexual consent and communication; attitudes toward condom and contraceptive use; power balance and experiences within sexual relationships; and knowledge of health care rights, educational rights, service locations, and financial literacy. Outcomes will be assessed at 3- and 9-month postintervention follow-ups.

Multimedia Appendix 2 [50-57] highlights our primary and secondary measures, with sample survey items.

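### The primary outcome is labelled contraceptive use but counts abstainers as successes, so a positive result alone cannot show that condom or contraceptive use changed

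*Protocol article*

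**What the plan says.** All references are to the protocol article.

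- **Primary Outcome** introduces the outcome as an effect on contraceptive use. It then defines it as the prevalence of participants "who report either abstaining from sex or using c condoms during vaginal or anal sex" in the past 3 months, assessed at the 3-month follow-up. As worded, this covers all participants, and abstainers count as successes.
- **Textbox 1, primary question and secondary question 1**, put the same outcome among those who had vaginal or anal sex in the past 3 months.
- **Textbox 1, other behavioural questions.** Question 2 asks about the effect of the "intervention on rates of condomless vaginal or anal sex", with no scale or denominator. Question 9 concerns condom errors.
- **Secondary Outcomes** lists "condom use behaviors, condomless sex, and condom errors" among the outcomes, assessed at 3 and 9 months, and refers to Multimedia Appendix 2 for the measures. That appendix is not among the documents at hand.
- **Table 1** describes a contraception module that begins with "Condom use and steps; common methods of birth control". Other modules cover sexual and personal boundaries and affirmative consent. No lesson is described as being on abstinence.

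**The concern.** The label and the definition do not match. A youth who has no sex in the 3-month window is a success without having used any contraceptive. The composite therefore adds two behaviours that can move separately or in opposite directions, while the label credits the sum to one of them.

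What is at stake is the sentence the trial may write at the end. If the composite improves, the plan's wording invites the conclusion that contraceptive use improved, even if condom use among sexually active youth did not change. Conversely, a rise in condom use accompanied by a rise in sexual activity could leave the composite flat and be read as no effect on contraception.

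**Working it through.** **1. The plan's detectable effect.** Inputs from Sample Size and Power Analyses: 500 randomised 1:1, 25% attrition (500 × 0.75 = 375 analysed), 5% type I error, "2-sided hypothesis test", 80% power, outcome prevalence 50%, and 25% of variance explained by covariates.

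- Effect size = (z₀.₉₇₅ + z₀.₈₀) × √(4(1 − R²)/N) = (1.960 + 0.842) × √(4 × 0.75/375) = 0.251 SD.
- On the probability scale: 0.251 × √(0.5 × 0.5) = 0.125.

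This agrees with the upper part of the range in Overview of Analytical Strategy (0.11 to 0.13, or 0.23 to 0.25 SD) and with that section's example of 50% against 37.5%, a difference of 12.5 points. I use 12.5 points below.

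**2. The composite split into its parts.** Let *a* be the share with no vaginal or anal sex and *c* the condom share among the sexually active.

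- Success = a + (1 − a)c
- Condom-protected sex = (1 − a)c
- Condomless sex = (1 − a)(1 − c) = 1 − success

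By the last line, a yes/no condomless-sex outcome over all youth is the exact complement of the composite and adds nothing to it.

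**3. Two routes to 62.5%.** Assumed control split: 30% abstinent, 20% condom-protected, so c = 0.20/0.70 = 28.6%.

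- Less sex only, c fixed: 1 − a = 0.375/(1 − 0.286) = 0.525. Abstinent is 47.5% and condom-protected is 0.525 × 0.286 = 15%.
- Condom use only, a fixed: condom-protected is 62.5 − 30 = 32.5%, and c = 0.325/0.70 = 46.4%.

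| | Control | Less sex only | Condom use only |
|---|---|---|---|
| No sex | 30% | 47.5% | 30% |
| Sex with condoms | 20% | 15% | 32.5% |
| Condomless sex | 50% | 37.5% | 37.5% |
| Composite | 50% | 62.5% | 62.5% |
| Condom share among active | 28.6% | 28.6% | 46.4% |

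**4. Other assumed splits**, each with the composite going from 50% to 62.5%:

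| Control abstinent / condom-protected | Less sex only: abstinent / condom-protected | Condom use only: abstinent / condom-protected |
|---|---|---|
| 10% / 40% | 32.5% / 30% | 10% / 52.5% |
| 20% / 30% | 40% / 22.5% | 20% / 42.5% |
| 40% / 10% | 55% / 7.5% | 40% / 22.5% |

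Condomless sex is 37.5% in every case.

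**5. The offsetting pattern.** From the 30/20 split, abstinent 20% with condom-protected 30% still gives 50%, although the condom share among active youth has risen from 28.6% to 30/80 = 37.5%.

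**6. What a measure among active youth would show.** Condomless sex among the sexually active is 100 − 28.6 = 71.4% under less sex only and 100 − 46.4 = 53.6% under condom use only. That would tell the routes apart, but it selects youth on a behaviour after randomisation that the programme may change, so it is not a clean intention-to-treat contrast.

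**The case against.** **Other outcomes may separate the routes.** A reader might infer that nothing planned can distinguish less sex from more condom use. The documents do not support that. Secondary Outcomes names condom use behaviours separately from condomless sex and condom errors, at both follow-ups. The condomless-sex rates have no stated denominator, and among active youth they would separate the routes. The measures are in an appendix that is not shown. The list in Secondary Outcomes does look like a condensed Textbox 1, which would leave only the composite to match condom use behaviours. That is an inference, and the timing differs: 3 and 9 months there, 9 months only in secondary question 1. What stands is narrower: no question in Textbox 1 names abstinence alone or condom-protected sex alone, and the article does not define the outcomes that might fill the gap.

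**The denominator conflict comes first.** Under Textbox 1's restriction to those who had sex in the window, abstinence over that window could not contribute and the less-sex route could not arise. This stands. The point rests on the wording in Primary Outcome, and the two places must be reconciled.

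**The composite is a legitimate target.** The programme aims to reduce unintended pregnancy and sexually transmitted infections, and both routes serve that aim. If condomless sex does not change, a null is the correct answer to the composite question. This also stands. The objection is to the contraceptive-use label, not to the composite.

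**Component tables usually belong in the SAP.** Agreed: their absence from a condensed article is not itself a fault. The mismatch between label and definition, and the conflicting denominators, are in the article's own text.

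**The fall in condom-protected sex is partly mechanical.** Correct. From 20% to 15% the condom share among active youth stays at 28.6%, so this should not be read as worse condom use.

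**Conclusion.** The point holds in a limited form. Under the all-participant wording of Primary Outcome, a positive composite result cannot by itself show that condom or contraceptive use changed. The full 12.5-point effect can arise with the condom share among active youth unchanged, and condomless sex measured yes/no over everyone is 37.5% by either route. The direction holds for every split tried, from 10/40 to 40/10. The splits are assumptions, and the pure routes are extremes chosen to show the range: under 30/20, the less-sex route needs abstinence to rise by 17.5 points. Some movement by that route is plausible, since Table 1 covers boundaries and consent.

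The validity of the primary test is not in question. What needs correcting is the claim attached to it, and the conflict over who is counted.

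**What to change.** Before the final analyses begin, which the Results section places after the last follow-up surveys (expected by March 2026):

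1. Reconcile the primary question and secondary question 1 in Textbox 1 with Primary Outcome, and state that the composite is analysed in all randomised youth whatever their sexual activity during follow-up.
2. Name the primary outcome as abstinence or condom use (avoidance of condomless sex), not contraceptive use.
3. Add one supportive intention-to-treat table at 3 and 9 months. Classify every youth as no vaginal or anal sex, sex with condoms, or condomless sex in the past 3 months. Give each share by arm, with arm differences and 95% confidence intervals from the same adjusted model. Do not restrict it to sexually active youth.
4. State in advance that the conclusion will mention condom use only if that component moved.

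The cost is one table from items already needed to build the composite, and it takes no alpha because it is supportive. The trial is sized for the composite, so the component contrasts are less precise for their purpose: if the effect is shared between routes, each component moves by less than the composite and its interval may include zero. The table also shows net shares, not which individuals changed, so its three rows should be read together.
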